### Intervention and Comparison

The case group is treated in the MSU, which is designed to establish a treatment unit integrating neurological symptom examination and CT diagnosis, achieving intravenous thrombolytic therapy and remote consultation at the first moment. During transportation, the physician can carry out neurological evaluation (NIHSS scores), blood glucose, coagulation index detection, and head CT scanning on the ambulance where data are transmitted to the stroke center in real time through 5G networks for technical support and treatment guidance from experts. Once the patient is recognized as suitable for thrombolysis, t-PA treatment will be given within the “golden time” of stroke management. The MSU team includes a paramedic, a stroke doctor, and a neuroradiologist, integrating the conventional EMS in a mixed urban–rural environment. The patient is evaluated for vital signs and neurological impairment followed by head CT screening and blood biochemical examination. The patients who meet the requirements of intravenous thrombolysis will be given t-PA treatment on the MSU vehicle after the informed consent is signed. Those who are not suitable for intravenous thrombolysis will be transported to the stroke center for further treatment. If necessary, remote consultation will be carried out through a customized telemedicine system based on 5G technologies. The MSU adopts a 7-day 24-h working system. In contrast, the control group is treated through conventional EMS in which the city emergency medical rescue center dispatches an ordinary ambulance. Head CT screening, blood biochemical examination, and the followed t-PA treatment (if suitable) will be performed after patients are delivered to the hospital’s emergency center (Nor et al., 2005) (see Figure 2).

**FIGURE 2 F2:**
[figure not shown]
Regular care life chain versus 5G-based SSES life chain.

### Primary and Secondary Outcomes

The primary endpoint is the utility-weighted modified Rankin Scale (uw-mRS) at 90 days assessed with a telephone interview. Secondary endpoints include time-dependent phenomena such as the alarm to CT scan completed time, the alarm to treatment decision time, the alarm to thrombolytic time, quality of life assessed with EQ-5D at follow-ups over 5 years, symptomatic intracranial hemorrhage combined with NIHSS score, as well as cost-effectiveness.

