### Participants

A total of 484 participants are recruited from the Ya’an people’s Hospital, 242 of whom were randomized to the intervention group and the rest randomized to the comparison group.

Each participant must meet all of the inclusion criteria to be enrolled in this study, which are given as follows:

1.Patients need to be aged over 18 years, with a final diagnosis of ischemic stroke.2.Patients’ confirmed onset-to-alarm time is less than 4.5 h.3.Patient is recognized as a t-PA candidate, with mRS scores less than 3.4.Patients volunteer to participate and sign an informed consent.

The exclusion criteria include uncertain symptom onset, no focal stroke-like symptoms, severe malignant, or pregnancy.

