### Statistical Analysis

We calculate the sample size by comparing two independent samples. A *t*-test compares the mean uw-mRS at 90 days and corresponding two-sided 95% confidence intervals if the assumption of normality is not valid. Although the mRS is a primary endpoint, the difference among the uw-mRS categories is significant, and the *t*-test assumption and central limit theorem are probably met. The calculation of uw-mRS will be adjusted for baseline uw-mRS and baseline covariates associated with mRS in a linear regression model. Stratified analyses of the primary outcome and pooled measures are conducted by the Cochran–Mantel–Haenszel analyses and multiple ordinal regressions. We use a proportional odds model to process dichotomized outcomes of uw-mRS 0-1 vs. 2-6 with binary logistic regression. Participants in the intervention group who give up during the program will be excluded from the analysis. In addition, subjects in both treatment groups will be excluded from the protocol analysis if any violations of the following protocols after randomization and during intervention and follow-up. All analyses are performed by SPSS 27.0.

Besides, we explore the missing data and compare the distribution of critical variables. Suppose there is a reasonable amount of missing data and the data summary indicates that the data are missing at random. In that case, all analyses will be performed after multiple imputations of missing data using baseline variables as auxiliary variables.

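### Requiring a final diagnosis of ischaemic stroke removes, in both arms, patients given t-PA who prove non-ischaemic, so the haemorrhage endpoint cannot show whether moving the t-PA decision to the vehicle changes that risk

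*Protocol article*

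**What the plan says.** **Entry (Protocol article, Participants).** The rule is strict: "Each participant must meet all of the inclusion criteria to be enrolled in this study". The first criterion is "Patients need to be aged over 18 years, with a final diagnosis of ischemic stroke". Being judged a t-PA candidate is a separate criterion. The exclusions are: "The exclusion criteria include uncertain symptom onset, no focal stroke-like symptoms, severe malignant, or pregnancy".

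**Treatment (Intervention and Comparison).** In the MSU arm, patients found suitable after on-board examination, blood tests and CT "will be given t-PA treatment on the MSU vehicle after the informed consent is signed". In the control arm, CT, blood tests and any t-PA "will be performed after patients are delivered to the hospital’s emergency center".

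**Endpoints (Primary and Secondary Outcomes).** The secondary list ends with "symptomatic intracranial hemorrhage combined with NIHSS score, as well as cost-effectiveness". No population is named for these items.

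**Analysis sets (Statistical Analysis).** Intervention-group participants who give up are removed from the analysis. In addition, "subjects in both treatment groups will be excluded from the protocol analysis if any violations" of the protocol occur after randomisation. Both rules take patients out; neither brings any in.

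**The concern.** Whether a patient belongs to the trial depends on something learned only after the treatment under study may already have been given. A patient can be a t-PA candidate at the time of decision, receive t-PA, and then turn out to have a mimic or a haemorrhagic stroke. Under the stated entry rule that patient was never a participant, so a bleed after t-PA is not counted and its cost does not enter the cost-effectiveness comparison.

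This matters here because the intervention changes where and when the t-PA decision is made. Whether that change leads to more, fewer or equally many non-ischaemic patients being treated, and what happens to them, is a natural safety question for decision-makers. Selecting on the final diagnosis means the trial's own haemorrhage endpoint cannot answer it.

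**Working it through.** **1. The plan's own figure.** The article gives no haemorrhage rate, no expected share of treated patients who prove non-ischaemic, and no size for this endpoint, so there is nothing to reproduce. The only figure used below is the 242 patients per group from Sample Size Estimation.

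**2. The sections side by side.**
- Participants: all criteria must be met, and one is the final diagnosis. Candidacy for t-PA is listed separately, so a patient can satisfy one and fail the other.
- Intervention and Comparison: t-PA follows the examination, CT and blood tests, in the vehicle or in hospital. The article does not date the final diagnosis. That it can come after t-PA is inferred from the word final and from its separation from candidacy.
- The exclusion for lack of focal symptoms does not cover a mimic or a haemorrhagic stroke with focal symptoms. None of the exclusions keeps a treated patient for safety.
- Primary and Secondary Outcomes and Statistical Analysis name no wider set that restores these patients.

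Conclusion from the text: t-PA given, then a non-ischaemic final diagnosis, means not a participant and not counted, in either arm.

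**3. Illustration on assumed values.** Assume all 242 retained patients in an arm received t-PA and about 3% bled: 0.03 × 242 = 7.3, taken as 7, so 7/242 = 2.89%. Let m be the assumed share of treated patients who are finally non-ischaemic. The number omitted is k = 242 × m/(1 − m). With x haemorrhages among them, the all-treated rate is (7 + x)/(242 + k).

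| m (assumed) | k | x = 0 | x = 1 |
|---|---|---|---|
| 2% | 5 | 7/247 = 2.83% | 8/247 = 3.24% |
| 5% | 13 | 7/255 = 2.75% | 8/255 = 3.14% |
| 10% | 27 | 7/269 = 2.60% | 8/269 = 2.97% |
| 15% | 43 | 7/285 = 2.46% | 8/285 = 2.81% |

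The all-treated rate exceeds the reported one only when x/k is above 7/242 = 2.89%. Omitted patients who seldom bleed would bring it down, and omitted patients who bleed often would push it up. The same point in rates, with 3% in retained patients and m = 5%: 0.95 × 3% + 0.05 × 0.5% = 2.9% if the omitted bleed at 0.5%, and 0.95 × 3% + 0.05 × 30% = 4.4% (4.35%) if they bleed at 30%.

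**4. Between arms.** If both arms omit 13 patients with one bleed each, the comparison is 8/255 against 8/255, and the difference of zero seen in 7/242 against 7/242 is right. If only one arm has that bleed, the true difference is 8/255 − 7/255 = 1/255 = 0.39 percentage points where the trial reports zero. The article gives no ground for saying which arm that would be.

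**The case against.** The strongest reply is that the outcomes section merely lists the endpoint, and that an article may leave a safety population to the full protocol or SAP. That would dispose of the point if the article were only silent. It is not silent: it states an entry criterion, and a later document could count these patients only by overriding it. So the point rests on the entry rule in Participants; the endpoint list shows only where the effect falls.

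Several stronger readings are tempting and are not supported:
- *That this hides harm on the MSU specifically.* The entry rule filters both arms, and a control patient treated in hospital who proves non-ischaemic is omitted in the same way. Bias between arms needs a difference in how often such patients are treated, or in how often they bleed. The article gives neither, and nothing in it says the mobile scan is less accurate. It places a stroke doctor and a neuroradiologist on the vehicle, with remote expert support.
- *That haemorrhage is understated.* The table shows that the omission can move the rate either way.
- *That everyone harmed by a wrong treatment decision is lost.* Patients with ischaemic stroke who bleed after t-PA remain counted, unless the intervention-only rule on giving up removes them.
- *That each omitted event shifts the arm's rate by 1/242 = 0.41 points.* This adds the event but leaves the omitted patients out of the denominator. With 13 omitted, one event moves the rate from 2.89% to 3.14%, about 0.24 points.

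It is also fair to say that the exclusion for protocol violations probably describes a per-protocol set and is not stated to govern the haemorrhage endpoint. It is therefore only weak support; what counts is that no section restores the omitted patients.

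**Conclusion.** The point holds as a consequence of a stated rule. In both arms, a patient given t-PA whose final diagnosis is not ischaemic stroke is not counted for symptomatic intracranial haemorrhage or cost-effectiveness. As written, the trial cannot show whether more such patients are treated, or bleed, on the MSU than under regular care.

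Size and direction are unknown. On assumed shares of 2% to 15%, about 5 to 43 treated patients per arm would be left out, and with none or one of them bleeding an assumed 2.89% would become anything from 2.46% to 3.24%. More bleeds among them would take it higher. These ranges rest entirely on assumed inputs; the defect does not depend on them. It should be corrected, but it is a gap in what the trial can report on safety, not evidence of a hidden excess in either arm.

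**What to change.** State in Primary and Secondary Outcomes and in Statistical Analysis that symptomatic intracranial haemorrhage is reported by arm for every allocated patient who receives any t-PA, whatever the final diagnosis, withdrawal or protocol deviation. Report beside it, by arm, the number treated whose final diagnosis was not ischaemic stroke, and give the ischaemic-stroke subset as a further analysis. Add a sentence in Participants so that the final-diagnosis criterion does not override this reporting set, and say whether these patients' costs enter the cost-effectiveness analysis. The efficacy population need not change for this purpose.

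The cost is wording, one more table, and outcome records for a few treated patients who would otherwise be dropped. The haemorrhage rate may come out less favourable. No treatment rule or patient procedure is altered.

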### Sample Size Estimation

Previous studies suggested that the difference in mean 90d uw-mRS between groups ranged from 0.024 to 0.25. However, according to our pilot study data, we anticipate that the difference in 90d mean uw-mRS is 0.09 (0.59 vs. 0.50) with a standard deviation of 0.5 in both groups. Considering a type-I error of 0.05, a study power of 0.8, and a two-sided test, we included a total sample size of 484 participants after considering a 10% dropout rate, each group with 242 participants.

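### The planning SD of 0.5 is at or above the maximum for a 0-to-1 uw-mRS with the stated means, so it is implausible and should be recomputed from the pilot data, with the power of 484 patients restated

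*Protocol article*

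**What the plan says.** The protocol article defines the main outcome under Primary and Secondary Outcomes: "The primary endpoint is the utility-weighted modified Rankin Scale (uw-mRS) at 90 days assessed with a telephone interview". Sample Size Estimation gives the planning values as "the difference in 90d mean uw-mRS is 0.09 (0.59 vs. 0.50) with a standard deviation of 0.5 in both groups" and attributes them to the trial's own earlier data ("according to our pilot study data, we anticipate"). The error rates follow: "Considering a type-I error of 0.05, a study power of 0.8, and a two-sided test". The result is stated as "we included a total sample size of 484 participants after considering a 10% dropout rate", which is 242 per group.

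Statistical Analysis compares the means by t-test and treats the outcome as having several levels: "the difference among the uw-mRS categories is significant, and the *t*-test assumption and central limit theorem are probably met". It also splits the scale at 0 to 1 against 2 to 6, so seven underlying categories are in view. The article gives no utility weight for any category and no range for the weighted score.

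**The concern.** A score with a floor and a ceiling cannot have an arbitrarily large SD. Once the mean is fixed, the SD is greatest when every patient sits at one of the two ends. An SD of 0.5 around means of 0.59 and 0.50 is about what a yes/no outcome would give. The uw-mRS assigns intermediate utilities to intermediate disability, so its SD should be visibly smaller.

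The SD is the input on which the stated power for the primary endpoint rests. If 0.5 does not describe the endpoint, the stated 80% power has no sound basis. Neither has any corrected sample size or power that reuses 0.5.

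**Working it through.** **Inputs.** From Sample Size Estimation: means 0.59 and 0.50, difference 0.09, SD 0.5 in each group, two-sided alpha 0.05, power 0.80, 10% dropout, 484 in total (242 per group). Evaluable per group after dropout: 242 × 0.90 = 217.8, taken as 218. Assumption, because the weights are not printed: utilities run from 0 to 1.

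**Step 1: the plan's own figure.** For two means, n per group = 2 × SD² × (1.960 + 0.842)² / difference² = 2 × 0.25 × 7.849 / 0.0081 = 484.5, so 485 per group.
- Total before dropout: 2 × 485 = 970.
- Total after dropout: 485 / 0.90 = 539 per group, 1078 in total.

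The printed 484 is not reproduced as a total. It matches the number per group before dropout.

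**Step 2: the ceiling on the SD.** On a scale from min to max, SD ≤ sqrt((max − mean)(mean − min)). On 0 to 1:
- mean 0.59: sqrt(0.41 × 0.59) = 0.492;
- mean 0.50: sqrt(0.50 × 0.50) = 0.500, reached only if half the patients score 0, half score 1 and nobody has an intermediate utility.

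The planning SD exceeds the first ceiling slightly and equals the second.

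**Step 3: when could 0.5 hold?**
- *Negative floor.* With a maximum of 1 and mean 0.59, SD 0.5 needs 0.25 ≤ 0.41 × (0.59 − min), so min ≤ 0.59 − 0.25/0.41 = −0.02. The ceilings for means 0.59 and 0.50 are 0.532 and 0.548 at a floor of −0.1, and 0.569 and 0.592 at −0.2.
- *Rounding.* The SD has one decimal and the means have two. An SD of 0.45 to 0.49 would print as 0.5. With illustrative weights 1, 0.91, 0.76, 0.65, 0.33, 0, 0 (assumed, not from the article), a split of 30/20/4/3/3/15/25% over mRS 0 to 6 gives mean 0.54 and SD 0.46. All seven levels are occupied, but 40% of patients are in the two worst ones.
- Other illustrative distributions with the same weights and means of 0.47 to 0.58 gave SDs from 0.34 to 0.46.

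**Step 4: what the SD does to 484 patients.** Two-sided 5% test, difference 0.09, normal approximation:

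| SD | Power, 218 per group | Total needed for 80%, with 10% dropout |
|---|---|---|
| 0.335 | 80% | 486 |
| 0.35 | 77% | 530 |
| 0.39 | 67% | – |
| 0.40 | 65% | 692 |
| 0.45 | 55% | 874 |
| 0.46 | 53% | – |
| 0.50 | 47% | 1078 |

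The SD at which 218 per group gives exactly 80% power is 0.09 × sqrt(218/2) / (1.960 + 0.842) = 0.335. If all 242 per group were evaluable, it would be 0.353. At SD 0.5 with 218 per group, the difference detectable with 80% power is 0.5 × 2.802 × sqrt(2/218) = 0.134, not 0.09.

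**The case against.** A reader might infer that an SD of 0.5 is mathematically impossible here. The document does not support that. It never states the range of the utilities, and an article may leave the weights to the full protocol. A slightly negative worst-state weight removes the impossibility. At a floor of −0.2, SD 0.5 does not even need nearly everyone at the extremes: with mRS 5 weighted −0.2, death 0 and the other illustrative weights unchanged, a 35/25/4/3/2/26/5% split gives mean 0.58 and SD 0.52. Rounding matters too, since a seven-level outcome with SD 0.46 would print as 0.5. Nor does the ceiling at mean 0.50 require mRS 1 to 5 to be empty. It requires only that intermediate utilities be unused, and a category weighted 0 could still be occupied.

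A reader might also infer that the implausible SD makes the trial too small. It does not. An SD that is too large asks for more patients than needed and is conservative by itself. The power shortfall comes from the per-group figure being used as the total. The final confidence intervals will in any case rest on the observed SD, not the planning one.

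These points stand and limit the claim to implausibility. They do not rescue the planning statement. The conservatism is not realised, because 484 in total was not derived correctly from 0.5. Repairing only the per-group/total error while keeping 0.5 would give 1078 in total, or 47% power at 484, both resting on a doubtful SD.

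**Conclusion.** The concern holds in limited form. On a 0-to-1 scale the planning SD is at or above its maximum for both groups (0.492 and 0.500) and is implausible for a multi-level outcome. It is tenable only as a rounded 0.45 to 0.49 with a very polarised outcome mix, or with a worst-state weight of about −0.02 or lower.

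The stated 80% power for a difference of 0.09 with 218 evaluable per group needs an SD of about 0.335 or less. Between SD 0.39 and 0.46, power runs from 67% to 53%, and at the printed 0.5 it is 47%. So the true SD decides whether 484 patients give adequate power, and the article does not let the reader determine it. These figures assume equal SDs, 10% loss in each group and the unadjusted two-sample comparison.

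**What to change.** In Sample Size Estimation, replace 0.5 with the SD of the 90-day uw-mRS recomputed from the pilot patients' mRS categories, using the trial's utility weights. State it to two decimals, with the weights or at least their minimum and maximum. Check it against sqrt((max − mean)(mean − min)) in each group. Then restate the power, or the detectable difference, that 484 patients in total give at that SD after 10% dropout. Do this together with the correction of the per-group/total error, because neither correction is complete without the other.

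Enrolment need not change. The work is a recalculation from data the sponsor says it holds and a revised sentence or two. The cost is that the restated power may be below 80%.

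### The stated inputs require about 485 evaluable patients per group, but the plan gives 484 as the total; under those inputs power is about 47%, not 80%.

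*Protocol article*

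**What the plan says.** All the inputs are in the Sample Size Estimation section of the protocol article. The expected effect, attributed to pilot data, is that "the difference in 90d mean uw-mRS is 0.09 (0.59 vs. 0.50) with a standard deviation of 0.5 in both groups". The error rates are given as "Considering a type-I error of 0.05, a study power of 0.8, and a two-sided test". The conclusion is that "we included a total sample size of 484 participants after considering a 10% dropout rate, each group with 242 participants".

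The Participants section repeats the number ("A total of 484 participants are recruited") and assigns 242 of them to the intervention group. The Statistical Analysis section says the size was calculated by comparing two independent samples and names a t-test of mean uw-mRS at 90 days. The design behind the calculation is therefore stated as well.

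**The concern.** A difference of 0.09 against a standard deviation of 0.5 is a standardised effect of 0.18. An effect that small needs several hundred patients in each group, and 242 per group looked far too few. The printed total is also almost exactly what the formula returns for a single group. That suggests the per-group result was taken as the total and the dropout allowance was never applied.

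This paragraph is the only justification given for the trial's size. A reader is told that the chance of missing a true 0.09 benefit is 20%. If the stated inputs hold, that chance is about one half, and a non-significant result would say little about whether the mobile stroke unit works.

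**Working it through.** **Inputs** (Sample Size Estimation): difference δ = 0.09 (0.59 vs 0.50); SD σ = 0.5 in both groups; two-sided α = 0.05 (z = 1.960); power 0.80 (z = 0.8416); dropout 10%; equal allocation. Design (Statistical Analysis): two independent samples, comparison of means.

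**1. Attempt to reproduce 484 in total, dropout included**

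n per group = 2(1.960 + 0.8416)² σ² / δ² = 2 × 7.849 × 0.25 / 0.0081 = 484.5, so 485. The noncentral t calculation gives 485.5.

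- Total before dropout: 2 × 485 = 970.
- With 10% dropout: 485 / 0.9 = 539 per group, 1,078 in total. The cruder inflation 485 × 1.1 gives 534 per group, 1,068 in total.

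The stated 484 in total is not reproduced.

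**2. Other readings**

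| Reading | Result |
|---|---|
| One-sided test (contradicts the text) | 382 per group, 764 in total; 850 with dropout |
| Two proportions, 0.59 vs 0.50 | 480 per group; 502 with continuity correction |
| Per-group result taken as the total | 484.5: matches, but no dropout added |
| Factor 2 left out of the formula | 242.2 per group: matches, but no dropout added |

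Only the two faulty readings give the printed number. Neither leaves room for the 10% dropout said to be included.

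**3. Power of the planned size under the stated inputs**

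Power ≈ Φ(δ / (σ√(2/n)) − 1.960)

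- n = 242 per group (no dropout): standard error 0.5 × √(2/242) = 0.04545; 0.09 / 0.04545 = 1.980; Φ(0.020) = 0.508. The t-test gives 0.506.
- n = 218 per group (242 × 0.9 = 217.8): standard error 0.5 × √(2/218) = 0.04789; 0.09 / 0.04789 = 1.879; Φ(−0.081) = 0.468. The t-test gives 0.466.

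**4. Difference detectable with 80% power at SD 0.5**

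δ = 2.8016 × 0.5 × √(2/n)

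- 242 per group: 0.127 (0.128 by t).
- 218 per group: 0.134.

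**5. SD at which the stated size would be right for δ = 0.09**

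σ = 0.09 / 2.8016 × √(n/2)

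- 217.8 per group: 0.335.
- 242 per group: 0.353.

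Power at 218 per group for SDs between that value and the stated one:

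| SD | Power |
|---|---|
| 0.35 | 76% |
| 0.40 | 65% |
| 0.45 | 55% |
| 0.50 | 47% |

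**6. Is an SD of 0.5 plausible?**

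The article does not give the utility weights. If they lie between 0 and 1 (an assumption), the largest possible SD is √(0.59 × 0.41) = 0.492 at mean 0.59 and √(0.5 × 0.5) = 0.5 at mean 0.50. A value of 0.5 is then at the ceiling and implies nearly all-or-none outcomes. This is a reason to recheck the SD. It does not prove an error, since 0.492 rounds to 0.5 at the precision printed. Even with 0.492 in both groups, power at 218 per group is only 48%.

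**The case against.** The arithmetic is not in dispute, but four reservations deserve an answer.

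- **The 47% is conditional.** It is the power of an unadjusted comparison if the SD is 0.5. If the SD is the misprinted figure and the pilot value is near 0.335, then 484 is adequate. This stands: what is shown is that the printed figures are incompatible, not which of them is wrong.
- **The cause is inferred.** The article shows no working. A total mistaken for a per-group number, a missing factor of 2 and a wrong SD would all explain the result. This also stands, but the mismatch does not depend on the cause.
- **Rounding.** Values near the favourable edge of what rounds to the printed inputs (SD 0.45, difference 0.095) give 60% power with 218 per group and 64% with 242. Rounding does not close the gap.
- **Covariate adjustment.** The Statistical Analysis section plans a linear model with baseline uw-mRS and other covariates, which could raise power. With R² of 0.2 to 0.3, power at 218 per group is 55% to 61%. Reaching 80% needs R² of about 1 − (0.335/0.5)² = 0.55, or about 0.50 without dropout. The sample size section claims no such gain, and the calculation is said to rest on two independent samples. The planned multiple imputation likewise does not restore the shortfall, since power is only 51% even with all 242 per group observed.

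Condensing a full protocol into an article does not explain the discrepancy either. The inputs and the result are all printed, and the total appears in two sections.

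**Conclusion.** The concern holds. Under the plan's own inputs, 80% power for a 0.09 difference needs about 485 evaluable patients per group, or about 1,078 randomised with 10% dropout. The plan has 242 per group. That gives about 51% power with complete follow-up and about 47% with the planned dropout, and a detectable difference of about 0.134 rather than 0.09.

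The result rests on the printed difference, SD, alpha and power, and on the unadjusted two-sample comparison that the article names. It does not depend on the 0-to-1 utility scale, which bears only on whether the SD is believable. It would change if the true SD were well below 0.5, but then the printed SD is wrong and the paragraph must still be corrected.

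**What to change.** Return to the pilot data, confirm the SD of uw-mRS, and then rewrite the Sample Size Estimation paragraph in one of these ways:

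1. **SD 0.5 confirmed, 484 kept.** State that power for 0.09 is about 47% with 10% dropout (51% without), or that 80% power applies to a difference of about 0.134.
2. **Pilot SD about 0.33 to 0.34.** Replace 0.5 by the observed value and show that 218 evaluable per group, 242 randomised, gives 80% power. The value must come from the pilot data and not be chosen to fit 484.
3. **0.09, SD 0.5 and 80% all kept.** The size becomes about 539 per group, 1,078 in total.

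The figures 0.09, 0.5, 80% and 484 should not be left side by side. Align the Participants section, and the registry entry if it carries the same numbers.

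The first two options cost only restated text and need no extra patients, although the first states a less favourable power. The third more than doubles recruitment (1,078 / 484 = 2.2) and is listed because it is what the stated inputs imply.
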